### Intervention

#### Clinical intervention: the nvHAP bundle

The University Hospital Zurich nvHAP bundle was designed by an interprofessional and interdisciplinary group of experts. Elements were chosen based on the evidence, although scarce, of their effectiveness and based on their anticipated feasibility and implementability. The bundle consists of five prevention measures (details see Additional file 1 nvHAP Bundle).

**1. Oral care**, i.e. mechanical oral care with or without pharmacological products, once daily in all patients, and three times daily in patients with swallowing difficulties.

**2. Prevention of dysphagia-related aspiration**, i.e. applying a ‘modified swallowing assessment’ (MSA) adapted from the ‘Standardized Swallowing Assessment’ by Perry et al. [20] (Additional file 2 ‘MSA Perry’) in a defined risk population, followed by further evaluation and treatment of dysphagia residing with the responsible physicians.

**3. Mobilization**, i.e. mobilization at least once at the day of surgery and at least twice daily in all other patients without contraindications.

**4. Stopping unnecessary PPI and antacids**, according to a list of indications in in-hospital guidelines.

**5. Respiratory therapy**, i.e. referral to respiratory therapists advised for a defined patient population, with a final decision at the discretion of the responsible physician.

All patients will be assessed regarding whether an active intervention of healthcare providers is indicated for each of the prevention measures at the following time points: after admission, after clinical deterioration, and after major surgery during. If yes, the prevention measure is executed according to the above description. The execution of the bundle element will be documented in the electronic medical record (EMR).

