#### Outcomes

##### Effectiveness outcomes

The primary outcome is nvHAP incidence rate, defined as the number of patients suffering from nvHAP per 1000 patient days per month. Secondary outcomes are in-hospital mortality rate; length of stay; and adherence to individual bundle elements and the nvHAP bundle as a whole.

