#### Quantitative data collection

##### NvHAP surveillance

We apply the European Centre for Disease Prevention and Control (ECDC) definition criteria for pneumonia that are used in the ECDC point prevalence studies [27] (Additional file 3 ‘ECDC nvHAP definition’). In brief, the pneumonia definition comprises radiologic criteria, systemic symptoms (fever > 38 °, leukopenia or leukocytosis) and pulmonary symptoms (e.g. cough, sputum production). Pneumonia is defined as hospital-acquired, if symptoms start ≥48 h after admission. If an invasive respiratory device was present in the 48 h preceding symptom onset, the pneumonia is considered a ventilator-associated pneumonia and thus not subject of this study. A validated semi-automated surveillance system for nvHAP is used [28]. Place of nvHAP acquisition is defined as department, ward and room to which the patient was affiliated 48 h before first symptoms of nvHAP, unless shorter incubation period is evident from patient history.

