##### Process indicators

Process indicators portraying adherence to the nvHAP bundle elements will be monitored in two ways. First, for all five prevention measures, at least one surrogate parameter for adherence is continuously extracted from the EMR of the *total patient population* (continuous process indicators; see Additional file 4 ‘Process indicators’). This parameter, e.g. tooth brushing provided by nurses, will be expressed per department, and month, and per hospital days. Second, we will monitor process indicators on a *sample basis* with individual assessment of a subset of 50 patients (denominator) at four different time points per department (intermittent process indicators; see Additional file 4 ‘Process indicators’). The latter allows a more detailed description of adherence, including non-documented prevention measures (e.g. oral care executed by patient) and takes into consideration the individual need of patients for the specific prevention measure (e.g. respiratory therapy is indicated only in a subset of patients). From the intermittent process indicators the ‘nvHAP adherence score’ will assess patient based adherence per department and time point. The score is based on samples of 50 patients, the ‘nvHAP adherence indicator’ takes the value 1 in the case the specific prevention measure was completed in the specific patient, 0 if that was not the case, and “empty” in the case of missing values. The ‘nvHAP adherence score’ is calculated by summing up the five proportions of patients with completed specific prevention measures (i.e. ‘nvHAP adherence indicator’=1) dividing it by factor five (Additional file 5 ‘nvHAP adherence score’).

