##### Analyses of process indicators

To portray adherence to the single prevention measures and the nvHAP bundle as a whole a descriptive analysis will be performed, summarizing continuous and intermittent process indicators and the ‘nvHAP overall adherence score’ by department-level periods. Further, we will evaluate whether the process indicators are associated with the nvHAP incidence rate. We will use GEEs with Poisson error and departments as clusters (as described above) to model the monthly nvHAP rates as dependent on either single continuous process indicators or on all continuous process indicators combined.

To model monthly nvHAP as dependent on intermittent process indicators (either single process indicators, all process indicators combined, or the nvHAP overall adherence score), we will use GEEs with Poisson error and departments as clusters (as described above). Because the intermittently collected process indicators are collected only at four time points, we will use linear interpolation to derive monthly values for these process indicators.

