## Discussion

With this mixed-methods study we will close critical knowledge gaps about the prevention of nvHAP, a neglected but common HAI. To date, literature about prevention measures against nvHAP is scarce [4], and our study will provide further knowledge by assessing the effectiveness of a five element prevention bundle against nvHAP on lowering nvHAP incidence rates. To our knowledge, it is the first study testing an inpatient bundle of nvHAP prevention measures on a broad patient population. Moreover, as effective implementation is as important as choosing the right bundle elements [14, 32], we place focus on a theoretically-informed implementation strategy.

The quantitative part of the study aims to not only measure the primary outcome parameter nvHAP incidence rate over time, but to also measure process indicators. This will help us to better understand if the implementation process was successful and to evaluate direct association between prevention measures and nvHAP incidence rate. As the nvHAP bundle cannot be effective if it is not well implemented, it is important to also measure implementation outcomes (e.g. acceptability, appropriateness, fidelity, and sustainability) as necessary preconditions for achieving the desired changes in clinical outcomes.

A major strength of this study is the mixed-methods approach, including an extensive formative qualitative study to provide insights about how and why departments succeeded, or faced challenges, in implementing the nvHAP bundle. With some notable exceptions [33–36], many qualitative implementation evaluations are limited to inquiries conducted at a single point in time. Such inquiries are prone to participant recall biases and may be insufficient to telling the whole implementation story [26]. Our longitudinal qualitative study aims to provide critical contextual insights to guide others hoping to implement the nvHAP bundle. Additionally, the participatory approach of our formative evaluation is intended to increase project commitment among stakeholders, particularly local implementation teams.

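### As described, the continuous process indicators include care given after nvHAP onset, which biases their association with nvHAP for measures that pneumonia can trigger

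*Protocol article*

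**What the plan says.** Under Process indicators, the Protocol article says that at least one surrogate for each of the five measures is "continuously extracted from the EMR of the *total patient population" and "will be expressed per department, and month, and per hospital days". Patients who already have nvHAP are therefore in both numerator and denominator.

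Under Analyses of process indicators, Poisson GEEs with departments as clusters are used "to model the monthly nvHAP rates as dependent on either single continuous process indicators or on all continuous process indicators combined". The outcome is "the number of patients suffering from nvHAP per 1000 patient days per month". No lag, pre-onset window or at-risk restriction is stated for the indicator.

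Under Clinical intervention, patients are assessed for each measure "after admission, after clinical deterioration, and after major surgery during" (the sentence breaks off there). Respiratory therapy is selective: "referral to respiratory therapists advised for a defined patient population, with a final decision at the discretion of the responsible physician".

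The outcome side is timed with care: "Place of nvHAP acquisition is defined as department, ward and room to which the patient was affiliated 48 h before first symptoms of nvHAP". The exposure side has no matching window. The limitations in the Discussion name only reporting bias for these indicators.

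**The concern.** A prevention measure can only act before the infection. As described, the indicator also counts care given after onset, and some of that care is given because of the pneumonia. A month with more cases then tends to show more respiratory therapy or swallowing assessment in the same department, whatever those measures do. This is reverse causation within a department over time, so department clustering and seasonal terms do not remove it.

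The analysis serves the third objective, and the Discussion expects it to "evaluate direct association between prevention measures and nvHAP incidence rate". The study has no control group, so readers will look here for evidence on which bundle elements work. An element that helps could appear not to.

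**Working it through.** **Inputs.** From the article: nine departments, monthly department counts, Poisson GEE with department clusters and sine/cosine terms. It gives no nvHAP rate, indicator level, post-onset stay or power figure for this analysis, so there is no stated figure to reproduce. Every other input below is an assumption.

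**Step 1. How far post-onset care moves an indicator.** Let r be nvHAP cases per 1000 patient-days, L the post-onset days per case, b the share of at-risk days with the measure, and q the share of post-onset days with it.

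- Post-onset share of days: f = (r/1000) × L
- Relative inflation of the indicator: f(q − b)/b

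Example: r = 1, L = 10 gives f = 0.01. With b = 0.05 and q = 0.50, inflation = 0.01 × 0.45/0.05 = 9%.

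| b, q | r 0.5, L 5 (f 0.25%) | r 1, L 10 (f 1%) | r 2, L 15 (f 3%) |
|---|---|---|---|
| 5%, 50% | 2.3% | 9% | 27% |
| 10%, 60% | 1.2% | 5% | 15% |
| 30%, 60% | 0.3% | 1% | 3% |
| 60%, 80% | 0.1% | 0.3% | 1% |

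The same can be put in records. One case with 7 post-onset days at 0.7 records per day adds 4.9 records. Against a background of 50/1000 × 1500 = 75 records in a month, that is 4.9/75 = 6.5%.

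**Step 2. Selective measure counted as records.** Assumed: 36 months, 1500 patient-days per department-month, 1 nvHAP per 1000 days, 7 post-onset days at 0.7 records per day, care rising 50% at staggered starts, and month-to-month log-SD of care 0.15. Ratios are per 50% more care. Results are for background care of 50, 100 and 200 records per 1000 days.

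Plain Poisson regression, departments not differing in background care, 300 data sets per setting:

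- No true effect: 1.29, 1.15, 1.08 (p<0.05 in 99%, 53%, 22% of runs).
- True ratio 0.80: 1.10, 0.95, 0.88. Pre-onset care only: 0.81 to 0.82. Preceding-month indicator: 0.88 to 0.89.

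Poisson GEE with department clusters (independence working correlation) and sine/cosine terms, true ratio 0.80, 100 runs per setting, by between-department log-SD of background care:

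| Background | SD 0 | SD 0.3 | SD 0.6 |
|---|---|---|---|
| 50 | 1.13 | 0.96 | 0.87 |
| 100 | 0.98 | 0.87 | 0.83 |
| 200 | 0.88 | 0.83 | 0.81 |

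A separate repeat gave 0.94 and 0.86 at SD 0.3 and 0.6 with low background care. With no true effect, that repeat gave ratios of 1.01 to 1.33 and significantly harmful results in 11% to 98% of runs. The pre-onset indicator gave about 1.00 and 1% to 9%.

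**Step 3. Measure counted as a share of days.** GEE with exchangeable correlation, 30 months, about 2000 patient-days per department-month, 150 runs, and only a small department difference in care (logit SD 0.2). Ratios are per 10% relative increase; a true 0.97 equals 0.97^(ln 1.5/ln 1.1) = 0.97^4.25 = 0.88 per 50%. Percentages in brackets are significantly harmful runs.

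| r, L, b, q | No effect, as described | No effect, pre-onset | True 0.97, as described | True 0.97, pre-onset |
|---|---|---|---|---|
| 1, 10, 5%, 50% | 1.049 (83%) | 1.000 (7%) | 1.025 (34%) | 0.976 (0%) |
| 1, 10, 10%, 60% | 1.034 (50%) | 1.002 (6%) | 1.006 (9%) | 0.975 (0%) |
| 1, 10, 30%, 60% | 1.015 (14%) | 1.003 (3%) | 0.986 (1%) | 0.971 (0%) |
| 1, 10, 60%, 80% | 1.011 (7%) | 1.001 (3%) | 0.983 (5%) | 0.968 (3%) |
| 0.5, 5, 5%, 30% | 1.017 (15%) | 0.998 (3%) | 0.991 (1%) | 0.976 (1%) |
| 2, 15, 5%, 50% | 1.059 (99%) | 1.000 (9%) | 1.037 (73%) | 0.974 (0%) |

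Even with pre-onset care, 8% to 17% of no-effect runs were significant in either direction, so tests with nine clusters are somewhat liberal. The harmful percentages should be compared with the pre-onset column, not with 2.5%.

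**The case against.** The strongest objection is about reach. A reader might infer that all five indicators rise with pneumonia and that a protective measure will generally look harmful. The documents do not support that. The route from pneumonia to more care is textual for reassessment after deterioration and plausible for selective measures. For a near-universal measure such as daily oral care, the indicator moves by at most about 1% and the estimate stays protective (0.983 against 0.97). Illness may lower mobilization, which would push the bias the other way. No route is shown for stopping proton pump inhibitors. Reversal also needs low background care and little contrast between departments, whereas the nine departments mix medical and surgical specialties. All of this stands.

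A second objection is that Additional file 4 (indicator definitions) and Additional file 6 (detailed model) are not shown and might contain a lag or an at-risk restriction. This also stands as a caveat. Still, the article itself specifies all patients, the aggregation and the model, and a restriction would qualify that wording.

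A third is that the intermittent samples of 50 patients take individual need into account and so protect the conclusion. This stands only in part: they enter separate models and leave the continuous-indicator models as they are. The Discussion offers them against reporting bias alone.

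Finally, the plan mostly speaks of association, not cause. That limits the stakes, but the stated purpose is to learn which measures are linked to less nvHAP, and this bias distorts that link.

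**Conclusion.** The point holds for the continuous-indicator models as the article describes them, and for selective measures that pneumonia can trigger (respiratory therapy, swallowing assessment). There it biases the secondary association analysis toward no benefit. On assumed inputs it yields excess harmful findings when there is no effect, and attenuates a true protective ratio, for example from 0.80 to between 0.81 and 0.98 in most settings. The ratio passed 1 in Step 2 only at the lowest background care with no difference between departments, and in Step 3 only for measures given on 5% or 10% of at-risk days with little department contrast.

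For near-universal measures the bias is small and mainly attenuation; for mobilization its direction is open. The before, during and after comparison of nvHAP rates uses no process indicator and is unaffected. The mechanism follows from the text. Every magnitude rests on assumed rates, stays and care levels, and the unseen additional files could narrow the point. The plan should be changed, but the main result is not at risk.

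**What to change.** 1. For the models in Analyses of process indicators that use continuous indicators, exclude nvHAP patients' care records and patient-days from symptom onset onward. Surveillance already determines onset.
2. Keep the all-patient indicator for the descriptive adherence summary.
3. Report the models with the preceding month's indicator as a sensitivity analysis only, and say that it is attenuated (0.88 to 0.89 against a true 0.80 in Step 2).
4. Name reverse causation beside reporting bias in the limitations. Say that care prompted by early deterioration, before recorded onset, may remain, and that the direction may differ by measure.
5. If Additional file 4 or 6 already sets such a restriction, state it in the article's text.

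Cost: no new data collection, but indicator records must be time-stamped and linkable to onset dates at patient level. The article says only that selected data are held in the data warehouse, so this should be confirmed first. Two versions of each indicator would then be reported.

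### A hospital-day denominator for all continuous process indicators mixes adherence with length of stay for any surrogate counted once per stay or per trigger, and can bias the adherence–nvHAP models

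*Protocol article*

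**What the plan says.** Under Process indicators, the protocol article states that "for all five prevention measures, at least one surrogate parameter for adherence is continuously extracted from the EMR" for the total patient population, and that this parameter "will be expressed per department, and month, and per hospital days". No other denominator is given for the continuous indicators. The one example, "e.g. tooth brushing provided by nurses", is a daily act. The surrogate chosen for each measure is in Additional file 4, which is not shown.

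Under Clinical intervention: the nvHAP bundle, oral care and mobilization carry daily frequencies. The swallowing assessment is applied "in a defined risk population, followed by further evaluation and treatment of dysphagia residing with the responsible physicians". Respiratory therapy is a "referral to respiratory therapists advised for a defined patient population, with a final decision at the discretion of the responsible physician". Need for each measure is assessed "after admission, after clinical deterioration, and after major surgery during" (the sentence breaks off there in the source).

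The outcome is nvHAP per 1000 patient days per month (Effectiveness outcomes). Under NvHAP surveillance, "Pneumonia is defined as hospital-acquired, if symptoms start ≥48 h after admission". Analyses of process indicators then uses GEEs with Poisson error "to model the monthly nvHAP rates as dependent on either single continuous process indicators or on all continuous process indicators combined". It names no length-of-stay or case-mix term.

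**The concern.** A day-based denominator fits a measure that is due on every day. It does not fit an act that follows admission or an event and is then complete, because the number of such acts per hospital day falls as stays lengthen even when every eligible patient is served.

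Two results are exposed. The first is the description of adherence by department and period, a secondary outcome: an apparent gain or loss may be only a change in length of stay, which is itself a secondary outcome. The second is the objective of relating adherence to nvHAP incidence. Predictor and outcome would both depend on length of stay, in opposite directions under simple assumptions, so a measure with no effect could appear protective.

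**Working it through.** The document gives no figure to reproduce here. The denominator, the 48 h rule, the patient-day outcome and the absence of a length-of-stay term come from the sections cited above. Every value below for adherence, stay, hazard and share at risk is an assumption.

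**Step 1: the indicator.** With adherence a, one trigger per admission and mean stay L days, the indicator per 1000 hospital days is 1000·a/L.

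**Step 2: the outcome.** With a constant hazard h after 48 h, nvHAP per patient day is h·(L−2)/L if stays are of fixed length, or h·exp(−2/L) if they are exponential.

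With a = 0.60 and h = 2 per 1000 at-risk days:

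| Mean stay (days) | Indicator per 1000 days | nvHAP per 1000 days, fixed stays | nvHAP per 1000 days, exponential stays |
|---|---|---|---|
| 4 | 150 | 1.00 | 1.21 |
| 6 | 100 | 1.33 | 1.43 |
| 8 | 75 | 1.50 | 1.56 |
| 10 | 60 | 1.60 | 1.64 |
| 12 | 50 | 1.67 | 1.69 |

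Adherence is the same in every row. Moving from 8 to 6 days lifts the indicator from 600/8 = 75 to 600/6 = 100. Adherence rising from 0.60 to 0.80 at 8 days gives the same value (800/8 = 100).

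A second example uses a = 0.50 and stays of 5 and 9 days. The indicator is 0.5/5 = 10.0 against 0.5/9 = 5.6 per 100 days, a 1.8-fold difference. The nvHAP rate ratio (5 against 9 days) is 0.60/0.778 = 0.77 for fixed stays, or 0.670/0.801 = 0.84 for exponential stays.

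**Step 3: the planned type of model with a null measure.** A Poisson GEE with an exchangeable working correlation was simulated with 9 departments, 36 months and 200 runs. Median stay was 7 days, with log-SD 0.30 between departments and 0.15 between months. Adherence was constant and had no effect on nvHAP.

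| Scenario | Rate ratio per SD of indicator | Runs significantly protective |
|---|---|---|
| One trigger per admission, constant hazard | 0.92 | 79% |
| Same, hazard rising as L^0.5 | 0.79 | 100% |
| No variation in stay | 1.00 | 4% |
| Need per admission proportional to L | 1.00 | 2% |
| Need per admission rising as L^1.5 | 1.07 | 0% |
| Hazard falling as L^−0.5 | 1.05 | 0% |

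The third row shows that the signal in the first comes from stay, not from the GEE. The last three show that it can vanish or reverse.

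**Step 4: sensitivity to other assumptions.** In a separate set-up (38 months, 1500 patient days per department-month, about 1 case per 1000 days, mean stays 5–9 days, ordinary Poisson model with one sine/cosine pair), the spurious rate ratio from the 10th to the 90th percentile of the indicator was 0.82–0.85, and 29–39% of runs were significant. With mean stays of 6–8 days it was 0.93 and 10%.

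The 5–9 day setting was also fitted as an exchangeable GEE (exponential stays, 150 runs per setting). There 39% of runs were significant, against 10% for an indicator free of the artefact. When departments also differed in baseline rate (log-SD 0.3), 17% were significant with the artefact and 17% without, although the mean rate ratio was still lower with it (0.90 against 0.98).

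**The case against.** The strongest objection is that the decisive input is not shown. The bundle section describes the measures, not the EMR surrogates. If the respiratory surrogate counts therapy sessions, or the dysphagia surrogate counts days on a precaution, hospital days are a sensible denominator and the problem does not arise. This stands, and it limits the point to surrogates that count an act once per stay or per trigger. It does not remove the point, because the text gives one denominator for all five measures and two of those are described as an assessment and a referral.

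A reader might infer that these indicators track length of stay instead of adherence, or that they will appear protective whenever adherence is constant. Neither follows. The quantity a/L moves with both terms. The protective direction needs stay to vary and triggers to grow less than in proportion to it. Deterioration and surgery triggers may well grow with stay, and Step 3 shows the bias then disappearing or changing sign. The formula in Step 2 also counts 48 h from department entry, whereas the protocol counts from admission and attributes a case to the department 48 h before symptoms, so transfers weaken it.

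The intermittent indicators take individual need into account and enter the same type of GEE, and the overall adherence score is built from them. This is a real safeguard, but a thin one: 50 patients at four time points per department, linearly interpolated to months. It leaves the separate models of the continuous indicators uncorrected. The Discussion offers it against documentation bias, not against this problem.

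**Conclusion.** The point holds in limited form. As written, the denominator makes adherence and length of stay inseparable for any continuous surrogate counted once per stay or per trigger, and the models that use it name nothing to separate them. A spurious association is a real risk and is probably protective under simple assumptions: rate ratios of 0.77 to 0.84 between departments with mean stays of 5 and 9 days, shrinking to about 0.93 across the indicator's 10th to 90th percentiles when stays range over 6–8 days. The shares of significant runs should not be read as forecasts, since they depend heavily on how much stay varies and on what else differs between departments.

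A reader might go further and conclude that the adherence–nvHAP objective as a whole will get a wrong answer, or that the effectiveness result is compromised. The document supports neither. The objective also has the need-based intermittent analysis, and both analyses under Analyses of nvHAP bundle effectiveness use no process indicator. What is affected is the description of adherence from the continuous indicators and their association with nvHAP. That justifies correcting the rule and is not a threat to the primary outcome.

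**What to change.** Tie the denominator to what each surrogate in Additional file 4 counts:

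- **Daily acts** (oral care, mobilization, and any surrogate that counts sessions or days): keep hospital days.
- **Once-per-stay acts:** use admissions to the department in that month, or patients entering the defined risk population where the EMR can identify them. The second is better because all admissions still move with case mix.
- **Acts triggered by deterioration or surgery:** use the number of trigger events. Admissions would be wrong here, since triggers can recur within a stay and the ratio could then rise with length of stay.

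Use these versions in the period summaries and the GEEs. In addition, or instead where a trigger cannot be counted, add mean length of stay per department-month to the models. The denominator change is the cleaner of the two, because length of stay is a secondary outcome that the bundle may itself alter. With one trigger per admission the corrected indicator equals adherence (0.60 in the example) at any length of stay.

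The cost is small. Admissions are needed for the length-of-stay outcome anyway. The additions are a counting rule for patients transferred between departments and, if used, one extra covariate.
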